**SMOKING MEASURES:**				
Current smoking and quit attempts	X	X	X	X
7 day point prevalence abstinence (self-reported)		X	X	X
6 month prolonged abstinence (primary outcome)				X
CO Monitoring (those reporting abstinence)				A
Heaviness of Smoking Index	X	S	S	S
Tobacco types	X			
Cost	X	S	S	S
History (age first smoked)	X			
Social influences	X			
Cravings	X	X	X	X
Smoking use motives	X			
Situations not allowed to smoke		X	X	X
Goal	X			
Motivation to quit	X	S	S	S
Confidence to quit	X			
Self-efficacy		X	X	X
Products/services to help quit (including NRT, Quitline)	X	X	X	X
Nicotine replacement products (helpfulness, likely use)	X			
Counseling preference (in person or telephone)	X			
Minnesota Nicotine Withdrawal Scale (only two items in follow ups)	X	X	X	X

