#### Primary Outcome

The primary outcome is defined as continued abstinence from smoking since the end of the treatment period, i.e., 6 months sustained abstinence, with no relapse (defined as 7+ days of continuous smoking, and no reported smoking in the last week), with biochemical verification at 8-month follow-up. Sustained abstinence will be assessed via the following question: “When did you last smoke a cigarette, even a puff?” If a participant reports prolonged abstinence at the 8 month follow up, and no smoking in the last week, they will be asked to attend a face to face visit to complete CO testing for objective validation using a Micro+ Smokelyzer, with a reading of 8 ppm or higher defined as indicative of recent smoking.

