#### Secondary Outcomes

##### Smoking

Secondary outcomes assessed at 2-, 5-, and 8-months post baseline will include:
7-day point prevalence abstinence, based on “Have you smoked at least part of a cigarette in the last 7 days?”Reported cigarettes smoked per day (for daily smokers) or cigarettes per week (for non-daily smokers).Expenditure on cigarettes.Number of quit attempts of 24 h or more, 1 week or more, and 1 month or more in the previous 3 months or since last assessed.Time to relapse: in those who do relapse will be determined by asking when they first smoked after a quit attempt.Number of subsequent quit attempts among those who relapsed.Hospitalizations and other intensive health service use.Financial stress questions adapted from Siahpush and Carlin (46).Productivity impacts (time off work or other duties).

Heaviness of Smoking Index (HSI): Nicotine dependence is assessed using this two item Index (47, 48). It uses a six-point scale calculated from the number of cigarettes smoked per day (1–10, 11–20, 21–30, 31+) and the time to first cigarette after waking (≤5, 6–30, 31–60, and 61+ min). Nicotine dependence is then categorized into a three-category variable: low (0–1), medium (2–4), and high (5–6). The HSI has been found to have good reliability and reasonable predictive validity (49).

Cravings: assessed by one item taken from the International Tobacco Control (ITC) Four Country Survey (50, 51), “Currently, how often do you get strong cravings to smoke tobacco?” with the response options of: (1) Hourly or more often; (2) Several times per day; (3) At least once a day; and (4) Less than daily. Difficulty in coping with situations in which smoking is not allowed is also assessed, on a 4-point Likert Scale from “very,” “moderately,” “mildly” to “not at all difficult.”

Withdrawal symptoms: as assessed by the Minnesota Nicotine Withdrawal Scale [MNWS; (52)], an eight item ordinal scale rating withdrawal symptoms from 0 (not present) to 3 (severe). At baseline the MNWS is administered, with two symptoms (concentration and appetite) assessed at follow-up. The MNWS has been shown to have good reliability and predictive validity (53).

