### Randomization

Following completion of the baseline assessment, a brief intervention will be delivered by a peer worker—prior to randomization—to ensure all participants receive the recommended minimum standard care, in a manner that is unbiased by the outcome of randomization. Following this, the computer program used to complete the baseline will randomize to condition using 1:1 randomization. Participants will be randomly allocated to either no further intervention, or to be contacted by Quitline who will offer a targeted callback counseling intervention with NRT provided, over an 8-week period. As stated above, cluster randomization will be used in situations where risk of contamination is higher, such as residential services, stratified by short- or long-term residence, with 1:1 allocation. Individual randomization will be used in services where contamination of risk is lower, via permutated block sizes of 4 and 6 to avoid incomplete blocks, stratified for site. Participants will be allocated a unique computer-generated study number. Randomization will be independently managed by the trial epidemiologist (JA) and uploaded to a web-based data capture tool (Research Electronic Data Capture; REDCap) that will also have case report forms (eCRF) created for the project using REDCap.

Following randomization, those in the intervention group will be told of the additional supports they will be getting (see above). Controls will be simply told the session is over and reminded of when the first follow-up survey might be expected.

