### Statistical Methods

#### Primary and Secondary Outcomes

Independent and blinded statisticians from the CReDITSS Unit at the Hunter Medical Research Institute, Australia, supervised by [name], will conduct analyses of the primary and secondary outcomes.

Analyses will be carried out using a cluster randomized trial framework where the individuals (*n* = 150) are treated as clusters that contribute only one person, the short-term residential programs are clusters that contribute an average of 15 people each (10 programs × 15 people/program = 150 total) and the long-term programs are clusters that contribute 10 people each (6 programs × 10 people/program = 60). We will use a generalized linear mixed model (linear regression for continuous outcomes and logistic regression for dichotomous outcomes) to handle the clustering and the repeated measures at baseline, 2-, 5-, and 8-months; individuals will be modeled as random effects, cluster as a random effect, and group assignment as a fixed effect. Mixed models allow for missing data for the primary intention to treat analysis, but a sensitivity analysis using a worst case scenario (baseline value for continuous outcomes or relapse for dichotomous outcomes in case of missing value) will also be carried out.

Intervention participants who do not complete the intervention, and participants who miss an assessment follow-up time point, will be kept in the study and contacted for later assessments (unless they choose to withdraw from the follow-up assessments).

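### As written, the repeated-measures model pools the pre-randomisation baseline into the group effect, shrinking four-visit continuous secondary outcomes to 0.75 of a constant follow-up effect

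*Protocol article*

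**What the plan says.** Under Statistical Methods (Primary and Secondary Outcomes), the protocol article specifies a generalized linear mixed model, linear for continuous and logistic for binary outcomes, "to handle the clustering and the repeated measures at baseline, 2-, 5-, and 8-months". The terms it names are: "individuals will be modeled as random effects, cluster as a random effect, and group assignment as a fixed effect". The abstract gives the same list. Neither place names a time term, a group-by-time term, a baseline covariate or a stratification factor.

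Under Randomization, the order is "Following completion of the baseline assessment, a brief intervention will be delivered by a peer worker—prior to randomization". Residential clusters are randomised "stratified by short- or long-term residence, with 1:1 allocation"; people randomised individually are allocated "via permutated block sizes of 4 and 6 to avoid incomplete blocks, stratified for site".

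Table 1 schedules the Kessler-10, AQoL-8D and AUDIT-C at baseline and at 2, 5 and 8 months. Self-reported 7-day abstinence and self-efficacy are scheduled at the three follow-ups only. The primary outcome is determined once, "with biochemical verification at 8-month follow-up". For withdrawal, the Smoking outcomes section says: "At baseline the MNWS is administered, with two symptoms (concentration and appetite) assessed at follow-up".

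**The concern.** A baseline value taken before allocation carries no treatment effect. If it is a response and the arms are compared through one coefficient covering every visit, the estimate is pulled towards zero and the test loses power. The coefficient is also not the 8-month effect, the visit at which the trial's main comparison is made. The outcomes at stake are the continuous secondary ones on which the Anticipated Results section expects a significant benefit, including mental health, quality of life and alcohol use.

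Withdrawal raises a related issue: eight items are collected at baseline and two later, so the totals are not the same measure at all four visits.

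A separate, smaller matter is that allocation is stratified by type of residence and by site while the model names neither factor. Leaving out a factor that was balanced by design wastes the precision the stratification bought.

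**Working it through.** **Figures in the plan.** The article gives no figure for this dilution. Its sample size, used below for power, reproduces: with 1% vs 8%, two-sided 5% and 80% power, (1.960 + 0.842)² × (0.01×0.99 + 0.08×0.92) / 0.07² = 7.849 × 0.0835 / 0.0049 = 133.8, i.e. 134 per arm. Then 134 / 0.70 = 191.4, against the stated 191.

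**Inputs.** Four visits, one before randomisation, so the true arm differences are 0, d, d, d for a constant follow-up effect d. Attrition is 30% (Sample Size Determination). Exchangeable within-person correlation ρ is an assumption: 0.5, with range 0.3 to 0.7.

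**Complete data.** Under exchangeable correlation each visit has equal weight, so the group coefficient is (0 + d + d + d)/4 = 0.75d for any ρ. Adding only a time main effect leaves it at 0.75d: that term absorbs change common to both arms, while the arm difference is still one number for all visits.

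**With attrition.** A person with m visits contributes information m/(1+(m−1)ρ), and (m−1)d/(1+(m−1)ρ) to the numerator. At ρ = 0.5:

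| Visits m | Information | Numerator / d |
|---|---|---|
| 1 | 1.000 | 0 |
| 2 | 1.333 | 0.667 |
| 3 | 1.500 | 1.000 |
| 4 | 1.600 | 1.200 |

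- Loss spread evenly (10/10/10/70% with 1/2/3/4 visits): (0.0667 + 0.1000 + 0.8400) / (0.1000 + 0.1333 + 0.1500 + 1.1200) = 1.0067/1.5033 = **0.67**.
- All loss straight after baseline (30% with one visit, 70% with four): 0.84 / (0.30 + 1.12) = 0.84/1.42 = **0.59**.

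Over ρ = 0.3 to 0.7, the shrinkage is 32–34% for the first pattern and 38–44% for the second.

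**Measured against the 8-month effect** (set to 1, complete data):

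| Effect at 2, 5, 8 months | Coefficient | Relative to the 8-month effect |
|---|---|---|
| 0.33, 0.67, 1 (growing) | 2.00/4 = 0.50 | 50% too small |
| 1, 1, 1 (constant) | 3/4 = 0.75 | 25% too small |
| 1.5, 1.2, 1 (mild fade) | 3.7/4 = 0.925 | about 8% too small |
| 2, 1.4, 1 (faster fade) | 4.4/4 = 1.10 | 10% too large |

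**Power.** Take 134 per arm, complete data and no clustering, with d set so that the plain mean of the three follow-ups has 80% power. At ρ = 0.5 the variance of that mean is (1+2ρ)/3 = 0.667, so d = 2.802 × √(2×0.667/134) = 0.279 SD. The four-visit mean has variance (1+3ρ)/4 = 0.625, so the pooled coefficient has z = 0.75×0.279/√(2×0.625/134) = 2.17 and power 58%. A baseline-adjusted follow-up mean has variance 0.667 − 0.25 = 0.417 and power 94%. Over ρ = 0.3 to 0.7, the ranges are 57–61% and 87–99%.

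**Outcomes without a baseline response.** For 7-day abstinence and self-efficacy the responses are d, d, d and the pooled coefficient is d: no dilution. The primary outcome is a single 8-month result, so nothing is averaged.

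**The case against.** The strongest reply is that this is one sentence in a condensed article. It says how individuals, clusters and group are treated; it does not say that group is the only fixed effect or that a pooled main effect is the test. A model meant to handle repeated measures, with secondary outcomes described in the abstract as reductions and improvements, is compatible with a group-by-time analysis, and the full term list may be in an analysis plan that is not shown. This stands in part: one cannot say that the analysis will be run this way. But the article does not merely stay silent. It states baseline as a response and lists the model terms, in two places, and following that list gives the shrunken estimate.

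A reader might infer more than the document supports:

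- That all secondary effects are diluted. They are not: 7-day abstinence and self-efficacy have no baseline response. Confidence to quit is a separate item asked only at baseline.
- That the loss is always at least a quarter. That holds against the average follow-up effect. Against the 8-month effect it can be smaller or reversed if the effect fades, which is plausible because treatment ends at 8 weeks.
- That the primary analysis is biased. It has no baseline response.
- That leaving out the strata contributes to the dilution. In a linear model it does not; standard errors tend to be too large, which is conservative. In a logistic model it can move the odds ratio somewhat towards the null, but the article gives nothing with which to size that.
- That eight withdrawal items will be modelled against two. Table 1 openly marks the reduced set at follow-up, and the same two items can be taken from the baseline form.

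**Conclusion.** The point holds in limited form and should be corrected. Read as written, the model shrinks the group effect on continuous secondary outcomes measured at all four visits to 0.75 of a constant follow-up effect with complete data. With 30% attrition the figure is about 0.67 or 0.59, depending on when people are lost. The 0.75 needs only exchangeable correlation and a constant effect; the attrition figures also assume ρ = 0.5, no time term and the same loss pattern in both arms. Against the 8-month effect there is no fixed figure. The unnamed strata are a secondary matter of precision only. The conclusion concerns the stated specification; it does not show that a fuller plan repeats it.

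**What to change.** For outcomes with the same measure at baseline, state that the 2-, 5- and 8-month values are the responses and the baseline value is a covariate, with withdrawal scored at baseline on the two items used at follow-up. Include time and group-by-time as fixed effects and name the 8-month contrast as the one reported. Keeping baseline as a response with the arms constrained equal there, plus group-by-time, would also recover the effect. Outcomes without a common baseline measure take the same model without that covariate.

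Add randomisation setting (individual, short-term residence, long-term residence) as a fixed effect. Since the Setting section says the sites are not yet known, whether to add a site term can be left to the analysis plan.

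The cost is a sentence or two of wording and 2 (time) + 2 (group-by-time) + 1 (baseline) + 2 (setting) = 7 parameters beyond the single group term. All the data are already scheduled. The wording should be fixed while the analysts are still blinded, so that the contrast is not chosen after results are seen.

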## Abstract

**Introduction:** Although smokers with severe mental illnesses (SSMI) make quit attempts at comparable levels to other smokers, fewer are successful in achieving smoking cessation. Specialized smoking cessation treatments targeting their needs can be effective but have not been widely disseminated. Telephone delivered interventions, including by quitlines, show promise. However, few SSMI contact quitlines and few are referred to them by health professionals. Mental health peer workers can potentially play an important role in supporting smoking cessation. This study will apply a pragmatic model using peer workers to engage SSMI with a customized quitline service, forming the “Quitlink” intervention.

**Methods:** A multi-center prospective, cluster-randomized, open, blinded endpoint (PROBE) trial. Over 3 years, 382 smokers will be recruited from mental health services in Victoria, Australia. Following completion of baseline assessment, a brief intervention will be delivered by a peer worker. Participants will then be randomly allocated either to no further intervention, or to be referred and contacted by the Victorian Quitline and offered a targeted 8-week cognitive behavioral intervention along with nicotine replacement therapy (NRT). Follow-up measures will be administered at 2-, 5-, and 8-months post-baseline. The primary outcome is 6 months continuous abstinence from end of treatment with biochemical verification. Secondary outcomes include 7-day point prevalence abstinence from smoking, increased quit attempts, and reductions in cigarettes per day, cravings and withdrawal, mental health symptoms, and other substance use, and improvements in quality of life. We will use a generalized linear mixed model (linear regression for continuous outcomes and logistic regression for dichotomous outcomes) to handle clustering and the repeated measures at baseline, 2-, 5-, and 8-months; individuals will be modeled as random effects, cluster as a random effect, and group assignment as a fixed effect.

**Discussion:** This is the first rigorously designed RCT to evaluate a specialized quitline intervention accompanied by NRT among SSMI. The study will apply a pragmatic model to link SSMI to the Quitline, using peer workers, with the potential for wide dissemination.

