#### Rationale for Study Design

Due to the nature of the intervention under investigation (i.e., linking smokers to existing smoking cessation care options readily available in the community, quitline, and NRT) there is a high risk of contamination among residential services where participants are living under the same roof and hence may compare treatment received. Therefore, we will use a partial clustering design where cluster randomization will be used in situations where risk of contamination is particularly high (e.g., in residential services). Individual randomization will be used in settings where participants are approached individually (e.g., clinics). Conceptually, this can be considered as a cluster RCT where some clusters only contribute a single person (see statistical methods section). This is sometimes called a split-plot design (33).

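### For continuous secondary outcomes measured at baseline, the stated cluster and person effects cancel from change from baseline, so any residence-level variation in change is left out of the standard error

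*Protocol article*

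**What the plan says.** In the protocol article, Statistical Methods (Primary and Secondary Outcomes) specifies a "generalized linear mixed model (linear regression for continuous outcomes and logistic regression for dichotomous outcomes"), used "to handle the clustering and the repeated measures at baseline, 2-, 5-, and 8-months". Its random and fixed parts are listed in one clause: "individuals will be modeled as random effects, cluster as a random effect, and group assignment as a fixed effect". The Abstract repeats the same specification. Neither place names a visit term, a group-by-visit term or a cluster-by-visit effect.

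The same section gives the planned layout. The 150 individually randomized people "are treated as clusters that contribute only one person", short-term residences supply "10 programs × 15 people/program = 150 total", and long-term residences supply "6 programs × 10 people/program = 60". The Randomization section allocates residences as whole units, 1:1, stratified by short- or long-term residence.

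The Abstract words the continuous secondary outcomes as "reductions in cigarettes per day, cravings and withdrawal, mental health symptoms, and other substance use, and improvements in quality of life". Table 1 schedules current smoking, Kessler-10, AUDIT-C and AQoL-8D at baseline and at all three follow-ups.

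**The concern.** With baseline in the response vector, the natural treatment effect at 8 months is a group-by-visit contrast: the difference between arms in change from baseline. An effect that takes the same value at every visit cannot contribute to that contrast. The person effect drops out, which is harmless because people are the level at which residual noise is counted. The cluster effect drops out too, and that matters because residences are randomized whole. On this layout, 210 of the 360 planned people sit in only 16 residences.

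If some residences improve or worsen together after baseline, that shared movement is part of the uncertainty in the treatment comparison. The stated model pools it into independent residual noise. The standard error is then too small and p-values for these secondary outcomes are too optimistic. The Anticipated Results section expects significantly better results on these variables, so the p-values are likely to carry claims.

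**Working it through.** **Inputs from the article.** The layout is 150 singles, 10 clusters of 15 and 6 clusters of 10. The total is 150 + 150 + 60 = 360. (This differs from the recruitment target of 382, but nothing below depends on the difference.) Attrition of about 30% is from Sample Size Determination. The article gives no standard error, intraclass correlation or design effect for these outcomes, so there is no figure of its own to reproduce.

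**Assumption, not in the article.** Let r be the share of within-person variance common to a residence at a given visit. This equals the correlation of change between two residents of the same residence. It is shown for 0 to 0.10.

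**Step 1: the cancellation.** Write y = fixed part + u(cluster) + v(person) + e, with residual variance s². In y(8 months) − y(baseline), both u and v vanish. With 180 per arm, the model's variance for the between-arm difference in change is

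2s²(1/180 + 1/180).

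With s² = 0.5 (total variance about 1) this is 0.01111, so SE = 0.1054. A generalized least squares calculation on the full layout gives 0.1054 whether the cluster variance is 0, 0.05 or 0.20. The cluster effect therefore gives this contrast no protection.

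**Step 2: the true variance.** One arm holds 5×15 + 3×10 + 75 = 180 people. The sum of squared cluster sizes is 5×225 + 3×100 + 75 = 1500, and 1500/180 = 8.33. Hence

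true variance / model variance = 1 + (8.33 − 1)r = 1 + 7.33r.

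**Step 3: with 30% attrition spread evenly.** Cluster sizes become 10.5 and 7, with 52.5 singles per arm. The arm size is 126 and the sum of squares is 5×110.25 + 3×49 + 52.5 = 750.75. The ratio 750.75/126 is 5.96, so the variance ratio is 1 + 4.96r.

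**Step 4: type I error.** This is 2[1 − Φ(1.96/√ratio)] at nominal two-sided 5%.

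| r | Variance ratio, complete data | True SE (model SE 0.1054) | Type I error, complete | Simulated, complete | Type I error, 30% attrition |
|---|---|---|---|---|---|
| 0 | 1.00 | 0.1054 | 5.0% | 4.8% | 5.0% |
| 0.01 | 1.073 | 0.1092 | 5.9% | 6.0% | 5.6% |
| 0.02 | 1.147 | 0.1129 | 6.7% | 6.8% | 6.2% |
| 0.05 | 1.367 | 0.1232 | 9.4% | 9.5% | 7.9% |
| 0.10 | 1.733 | 0.1388 | 13.7% | 13.7% | 10.9% |

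The simulated column uses 20,000 null trials per setting.

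**Step 5: other readings of the fixed part (complete data, r = 0.01 to 0.10).** If baseline means are constrained equal between arms, the cancellation is only partial and type I error is 5.7% to 12.3%. If a single group term is estimated over all four visits, the cluster variance stays in its standard error and type I error is 5.1% to 5.6%. That term, however, averages the pre-randomization value into the treatment effect.

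**The case against.** The best counter-argument is that this is a condensed article. It says that cluster is a random effect. It does not say that the effect is an intercept, or that a cluster-by-visit component is excluded, and such detail often sits in an analysis plan that is not shown. The group-by-visit contrast is also inferred. Only group is named as a fixed effect, and words such as reductions and improvements in the Abstract may indicate direction rather than define a change score. The Secondary Outcomes section simply lists values at 2, 5 and 8 months.

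Part of this stands: the contrast is an inference, and a fuller plan may already contain the missing term. But the article does more than stay silent. It puts baseline among the responses, lists the random part, and presents this model as the way clustering is handled. On the literal alternative, a single group term, the standard error is nearly right but the estimate is diluted by baseline. Either reading needs the same repair.

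Two objections on size also stand. The correlation of change is assumed and may be zero. Complete-data figures ignore the protocol's own attrition, which lowers the error at every non-zero r.

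A reader might also take the design rationale, that "participants are living under the same roof and hence may compare treatment received", as evidence that residents change together. It does not show that. It concerns contamination and justifies randomizing residences whole. Shared change is plausible, but the article does not document it.

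**Conclusion.** The point holds for continuous secondary outcomes with a baseline value, on the plain reading of one constant effect per cluster and per person. The stated model then leaves residence-level variation in change out of the standard error of the change contrast. For r between 0.01 and 0.10, type I error is about 5.9% to 13.7% with complete data and about 5.6% to 10.9% with 30% even attrition. At r = 0 there is no inflation. These figures rest on the article's layout, an even split within strata and an assumed r.

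Two stronger conclusions are tempting and not supported. One is that the primary analysis is also too liberal for this reason. Prolonged abstinence is assessed once, at 8 months, and everyone smokes at entry, so there is no change from baseline in which the cluster effect could cancel. The other is that these secondary tests will certainly run well above 5%. That is true only towards the upper end of the assumed range. The change is worth making because it is cheap and the article gives no basis for taking r as zero.

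**What to change.** In Statistical Methods and the Abstract, for continuous outcomes measured at baseline, model only the 2-, 5- and 8-month values as responses. Enter the baseline value as a covariate, and include a person effect, a cluster effect and a cluster-by-visit random effect. Alternatively, keep baseline as a response and add a cluster-by-visit effect. In either case, state that the treatment effect is the 8-month group contrast from that model.

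Add a small-sample degrees-of-freedom correction, because only 16 residences are randomized. In a separate simulation on this layout (2,000 null trials per setting), an 8-month analysis adjusted for baseline with a cluster random effect and a z test still rejected 6.0% to 6.5% of the time.

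The cost is a change of wording, with no new data. There is one more variance component to estimate, and intervals will be somewhat wider than the stated model would report. For the change contrast with complete data, the factor is √(1 + 7.33r): about 1.04 at r = 0.01 and 1.32 at r = 0.10. If residences do not differ in change, the added component should be estimated near zero and little is lost.
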